### Randomisation

Eligible participants who consented to taking part in the study were randomised in a 1:1 ratio to the index group and a wait-list control condition (the latter being offered the intervention once the three waves of assessment have been completed). A minimisation process was used to ensure a similar distribution of participant characteristics between the two study groups in terms of child age (younger (23–25 months) and older (25–27 months) and sex. ND performed the minimisation process, using the MINIM software [48] on site, when participants consented to being part of the study and prior to completion of baseline assessments. ND then notified an isiXhosa-speaking research assistant of the allocation, and this assistant then privately explained the allocation to the participant. The allocation list is held by ND, and is inaccessible to any of the staff or partners involved in the assessment or coding.

### Intervention

The intervention is a group-based, dialogic book-sharing programme based on our previous programme [45, 46, 49]. The intervention consists of 60–90-min sessions run weekly for eight consecutive weeks. The programme is delivered to groups of three to six caregivers and their children. Each session focusses on different and incremental techniques for caregivers to apply during book-sharing. For the first six sessions there is a ‘book of the week’ that the carers take home to share with their child, and that they bring back the following week. In session 7 all the key principles are reviewed, and the child chooses which of the six books they want to take home for that week. During the final, eighth, session, there is a group discussion where caregivers are guided in reflecting on the programme and they discuss plans for continuing with their book-sharing – such as registering at a nearby children’s library or continuing to meet as a group. Session 8 ends with a graduation where caregivers are presented with a certificate of completion, a laminated card with a summary of the key lessons from the programme (on the back of which there is a picture of themselves and their child sharing a book), and a copy of each of the six books used in the programme. Table 1 details the content for each session. For the 6-month period following session 8, the facilitator visits each participant bi-monthly to deliver a new picture book and have a short encouraging conversation with the caregiver about their book-sharing.

**Table 1 Tab1:** Summary of intervention session content

Session	Session content
1	*Introduction to Book-sharing*
	Introduction and basic dialogic book-sharing skills part 1 – following the child’s lead, using a lively voice, setting up book-sharing routines
2	*Pointing and Naming*
	Basic dialogic book-sharing skills part 2 – pointing and naming, repeating, extending and elaborating on things that interest the child, finding opportunities for praise
3	*Naming and Linking*
	Asking ‘where/who/what’ questions, linking book content to the child’s own experience, finding opportunities to use actions (e.g. hugging, eating)
4	*Talking about Feelings*
	Helping the child understand the meaning of basic emotion terms: happy, sad, angry, scared. Discussing why book characters feel the way they do, using facial expression and tone of voice to convey a character’s feelings, linking feelings to the child’s own experience
5	*Talking about Intentions*
	Discussing why characters feel the way they do, asking what characters are thinking and intending, encouraging the child to be curious about what will come next in the story
6	*Talking about Perspectives*
	Helping the child understand that different people can see things differently, know different things, and feel differently about things
7	*Summary*
	Reviews of key principles from sessions 1–6
8	*Graduation Event*
	Certificates of completion are presented to participants along with summary take-home cards and a full set of the 6 books (from sessions 1–6). A group discussion about how to remain motivated about book-sharing and how to access children’s books (e.g. registering with the local library).

For the intervention sessions, caregivers sit in a semicircle facing the facilitator who sits at the front of the room with a laptop on which a PowerPoint is displayed. An area at the back of the room is laid out for the children with a set of soft toys and balls. The first part of each session is a group-based, instructive presentation of the week’s key book-sharing principles. PowerPoint slides are used to deliver particular learning points, accompanied by brief illustrative video clips. Towards the end of the presentation, the facilitator discusses the book of the week with the carers, highlighting how the book can be used at home and providing examples of how to apply the techniques covered in that session.

The second part of the session involves one-to-one mentoring with the facilitator. This takes place in a separate room, where the caregiver is asked to share the book of the week with their child, under the guidance of the facilitator. These sessions last for approximately 10 min, with the final few minutes dedicated to positive feedback and, where considered helpful,  modelling of book-sharing techniques. This session also includes a discussion between caregiver and facilitator about the book-sharing home routine, where the facilitator encourages the carer to spend at least 10–15 min a day sharing the book of the week with their child and practising the techniques learned that week.

### Intervention facilitators, training and supervision

The intervention is delivered by two isiXhosa-speaking women from Khayelitsha. Both these facilitators have experience delivering book-sharing training to mothers from the community, having been facilitators in our previous trial [45, 46], as well as in an earlier pilot study [49]. Each of the two facilitators is supported by an assistant during intervention sessions whose role is to look after the children, who also attend the sessions. The assistants were selected from the community, based on having previous experience working with young children.

Facilitator training for the current book-sharing intervention was held over a 2-day workshop, run by PC, LM and ND. This included a refresher session, when the content of the earlier programme was reviewed, including a review of the accompanying PowerPoint presentation materials and videos. This was followed by instruction on the new programme content and materials. First, the key principles of the new sessions (i.e. those concerning emotions, intentions and perspectives – see Table 1) were explained, and the accompanying illustrative videos viewed. This was followed by discussion between the trainers and facilitators, and any questions or uncertainties were resolved. During these discussions the facilitators also discussed ways in which the key principles of the new material could be explained and demonstrated in a culturally appropriate manner.

The second part of the facilitator training covered the one-to-one sessions where parents practise book-sharing with their children and receive feedback from the facilitator. This training specified the role that the facilitator needs to play during these sessions, covering principles of sensitive instruction, modelling, and providing positive support. Additionally, facilitators were instructed on how to incorporate into the one-to-one sessions the central take-home messages from the group session.

Finally, facilitators were briefed on monitoring and evaluation procedures, including tracking attendance, scheduling participants for sessions, and following up with participants who miss sessions. They were also given a refresher session on using the PowerPoint presentation materials on laptops. The assistants attended a 1-day training workshop run by ND that covered basic video camera skills, activities to do with the children, and roles and responsibilities during sessions – such as preparing refreshments, filming, watching over the children.

Regular supervision is provided throughout the intervention. The trial manager (ND) meets with the facilitators for 2 to 3 hours at the end of each week and reviews how the sessions that week went. During the first half of the meeting the two facilitators discuss aspects that went well, challenges, and logistical issues. They also identify particular participants who are experiencing difficulties in applying the programme with their child, and discuss the support these individuals may need in their next one-to-one session. The second half of the meeting involves preparation for the following week’s session. The group go through the PowerPoint slides, discuss specific examples or strategies to use, and make sure that the facilitators have no unanswered questions or queries about the forthcoming session. Finally, the group reviews the attendance records from the past week, and discusses plans for catch-up sessions for any participant who may have missed the session. Every intervention session is video-recorded, and one session each week per facilitator is checked by ND for delivery fidelity.

### Data collection

#### Data collector training

A team of three data collectors have been trained in the child assessments and caregiver interview questionnaires. Training was held over a 3-week period and followed a data collector manual developed by ND, LM and PC. All three data collectors had previous experience administering questionnaires and child assessments, including administration of some of the measures used in the present study. During the three assessment waves, ND makes regular checks, both in vivo and though examination of the videos made, to ensure fidelity of assessment administration. All data collectors were familiar with consent and referral procedures, as well as how to discuss potentially sensitive topics during interviews with caregivers.

#### Procedures

All 140 carer/child pairs are assessed on three occasions: at baseline, following the 8-week intervention, and 6 months post intervention. For the baseline assessment, caregivers are contacted by the data collection team, and the study is explained to them, including that participation is entirely voluntary. A suitable time for them to come in for assessments is arranged. A driver picks participants up from their home and brings them into the research centre located in central Khayelitsha. On arrival, participants are offered refreshments for themselves and their child. Consent is then explained again and caregivers provide consent for both themselves and their children. Assessments last for up to 2.5 hours. This comprises specific assessments of the child (e.g. Early Childhood Vigilance Task), interviewing the caregiver (e.g. Communication Development Inventory), and filming the caregiver and child in interactive tasks (e.g. book-sharing). There are frequent breaks for drinks and snacks and, if the child shows any signs of tiredness or distress, the session is interrupted or, if necessary, terminated. At the end of the assessment session participants are given a food voucher (rand equivalent of US$8) for a local grocery store to compensate them for their time. Similar procedures are followed for the subsequent two assessment waves. To minimise assessment bias, assessments of children and caregivers are being carried out by data collectors who are blind to group allocation. All coders of video data will also be blind to allocation. Participants are requested not to reveal their allocation to data collectors.

#### Retention

Provisions have been put in place to maximise participant retention. This includes phone calls to remind participants of scheduled assessments. Where necessary, members of the data collection team visit the participant’s house to discuss arrangements for assessments, making every effort to accommodate the caregiver – including holding assessments on Saturdays for caregivers who work during the week.

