### Study setting

The study is being conducted in Khayelitsha, a large peri-urban township on the outskirts of Cape Town, South Africa. It is characterised by high levels of poverty, unemployment and violence [47]. All assessments take place at the Prevention Research for Community, Family and Child offices at the Masiphulisane Community Development Centre. Intervention group sessions are held in a church hall connected to the Masiphulisane Centre.

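### Retention home visits are made by the data collectors who must stay blind, which may compromise assessor blinding at the two later assessments

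*Protocol article*

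**What the plan says.** Under Procedures, the protocol article states that "assessments of children and caregivers are being carried out by data collectors who are blind to group allocation", as its protection against assessment bias. It adds that "All coders of video data will also be blind to allocation" and that families are asked not to disclose their arm. Under Randomisation, the allocation list is kept from assessment and coding staff, and a research assistant explains the allocation to each family in private.

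Under Data collector training: "A team of three data collectors have been trained in the child assessments and caregiver interview questionnaires". Under Outcomes, two assessors complete the assessment of each dyad.

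Under Retention, phone reminders come first, and then, where this is needed, "members of the data collection team visit the participant’s house to discuss arrangements for assessments".

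Under Intervention, carers take a book home in each of the first six weeks and return it the next week. At session 8 they receive a certificate, a card bearing a picture of carer and child sharing a book, and "a copy of each of the six books used in the programme". The facilitator then delivers further books over the following 6 months. Wait-list families are offered the programme only after all three assessment waves (Randomisation).

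Under Study setting: "All assessments take place at the Prevention Research for Community, Family and Child offices at the Masiphulisane Community Development Centre", and "Intervention group sessions are held in a church hall connected to the Masiphulisane Centre".

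**The concern.** One stated procedure works against another. The people whose blindness the trial relies on are the people sent to homes, and after allocation those homes can differ visibly by arm. The two safeguards, a withheld list and a request not to disclose, control what staff are told. Neither controls what a visitor sees.

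At stake are child measures that depend on how an adult behaves in the room. In the two picture vocabulary tests the assessor prompts the child and takes the response. In the helping task the assessor is the adult who has lost her pen. An assessor who believes she knows the arm can, without intending it, prompt more, wait longer or score an unclear response more generously. A blind coder working later from video cannot undo a difference in prompting that has already occurred.

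Any exposure would also be uneven. Visits are made where phone contact is not enough, so they fall on families who are harder to reach.

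**Working it through.** The documents give no figure on blinding, so there is none to reproduce. The check sets the procedures side by side.

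1. **Are the visitors the assessors?** Retention names the data collection team. Data collector training describes that team as three people trained in both the child assessments and the caregiver interviews. No other member is described.

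2. **When does it matter?** Randomisation takes place at consent, before baseline assessments are complete, so a visit to arrange the baseline would normally precede allocation. The risk lies in visits before the post-intervention and 6-month assessments.

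3. **Is there something to see?** During the programme an intervention home holds one borrowed book at a time. After session 8 it holds six books, a certificate and a photo card, and later the delivered books as well. A wait-list home has received none of these from the trial before the 6-month assessment. A certificate or photo card seen in the home identifies the arm.

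4. **How often would a visitor assess the same dyad?** Assume the two assessors are drawn at random from the three collectors.
 - Possible pairs: C(3,2) = 3. Pairs that include a given visitor: 2. Probability = 2/3.
 - If two collectors have visited, only one has not, so at least one of the two assessors must be a visitor.
 - Nothing in the sections on data collection or outcomes keeps a visitor off that dyad.

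5. **Which primary outcomes are exposed?**
 - Mainly the Peabody, Expressive One Word and Bayley language tests and the helping task. The first two are stated for baseline and post intervention only, so their exposure is at the post-intervention wave.
 - Less so the Communication Development Inventory, the prosocial scale and the aggression subscale. The caregiver is the informant and knows the arm whoever visits.
 - Less so the prohibition and compliance tasks, which are coded from video by blind coders, and the attention task, a fixed 7-minute screen presentation scored as time attending.

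6. **How large could a bias be?** This cannot be derived from the documents. As an illustration resting wholly on assumption, let 10% to 30% of dyads be unmasked, and let knowledge of the arm shift the group difference among them by 0.2 to 0.4 SD.
 - Average bias = share unmasked × shift: 0.10 × 0.2 = 0.02 SD, up to 0.30 × 0.4 = 0.12 SD.
 - Against the planning effect of 0.50: 0.02/0.50 = 4%, up to 0.12/0.50 = 24%.
 - Two-sided t test at 5%, 64 per arm, no true effect. The approximate non-centrality is bias × √(64/2) = bias × 5.66, and the rejection probability is:

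| Bias (SD) | Rejection probability |
|---|---|
| 0.02 | 5.1% |
| 0.06 | 6.3% |
| 0.10 | 8.7% |
| 0.12 | 10.3% |

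The lower end is negligible and the upper end is not. The documents do not say where in the range the trial would fall, or whether it falls inside it.

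**The case against.** The strongest reply is that the article describes an opportunity and nothing more. Visits are made only when needed, alongside phone calls, and only to settle arrangements. Nothing says the visitor goes indoors or sees a book. The allocation list is withheld and families are asked to stay silent. The trial manager checks administration in person and on video, and a random 10% of videos is checked for fidelity. Much of the primary outcome set does not depend on this route.

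Most of this stands, and it limits the point to a risk. A reader might infer more in four ways, none of which the text supports:

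- **That the procedures do reveal allocation, so the trial is not assessor-blind.** The number of visits, and what is seen on them, are not given.
- **That seeing no books identifies a control family.** The items may be put away or out of view.
- **That assessors see who attends sessions because the hall is connected to the assessment site.** Entrances, sightlines and the timing of sessions relative to assessments are not stated. Day-to-day scheduling is also the kind of detail that an article leaves to the full protocol or the data collector manual.
- **That caregiver-reported outcomes are biased through these visits.** Those informants are unblinded in any case.

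The reply does not remove the conflict at its centre. The article fixes who makes the visits, and they are the people it needs to keep blind. Fidelity checks can catch gross departures from procedure, but they are not built to detect a small difference in warmth or patience between arms.

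**Conclusion.** The point holds as a risk created by a stated procedure: home visits by data collectors after randomisation may compromise assessor blinding at the post-intervention and 6-month assessments. It rests on two inferences, both likely but not stated: that a visitor would sometimes notice programme material, and that the assessors are drawn from the same three collectors who visit. Its reach is mainly the assessor-administered child language tests and the live helping task. Its size is unknown. The 0.02 to 0.12 SD illustration (about 5% to 10% false positives per test at 64 per arm) shows only what assumed inputs would produce and should not be quoted as an estimate. The connected hall adds a possible route but carries no weight without a timetable. The change is worth making because it is cheap and the blind supports several primary outcomes.

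**What to change.** Amend Retention so that, after randomisation, home visits to arrange assessments are made by existing staff who neither assess nor deliver the intervention (the driver, for example), or so that arrangements are made by phone. The session assistants are not suitable, because they are intervention staff.

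Add a fallback: a data collector who has visited a home after randomisation does not assess that dyad at later waves. With three collectors and two assessors per dyad, this works only while no more than one collector has visited a given home, so visits should be logged by collector.

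Where feasible, avoid holding sessions in the connected hall while assessments are under way. Optionally, have assessors record a guess of the arm at the end of each later assessment, so that the success of blinding can be reported.

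The cost is slightly less flexible scheduling, and visits by staff who know the assessment procedures less well. Sample size, outcomes and intervention are unchanged.

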### Outcomes

Outcome data are collected through the use of (1) direct child assessments, (2) video-recorded caregiver-child interactions, and (3) caregiver interviews. The caregiver interviews and child assessments used have all been translated into isiXhosa. The assessment of each carer-child pair is completed by two assessors. This comprises assessments of the child (e.g. attention assessment), interviewing the caregiver (e.g. assessing carer depression), and filming the caregiver and child in interactive tasks (e.g. while sharing a book). All outcomes are presented in Table 2.

**Table 2 Tab2:** Study outcomes. Description of data: list of all study outcomes

Outcome	Measure
Primary outcomes	
Child aggression	Child Behavior Check List (CBCL) aggression subscale
	Scores from coded videos of a prohibition and compliance task
Child prosocial behaviour	Strengths and Difficulties Questionnaire, prosocial subscale
	Prosocial helping task
Child language	MacArthur-Bates Communication Development Inventory
	Peabody Picture Vocabulary Test
	Expressive One Word Picture Vocabulary Test
	Bayley Scale of Language Development
Child attention	Early Child Vigilance Task
Secondary outcomes	
Child social understanding	Wellman and Liu Theory of Mind Scale
	Emotion recognition task
Parental sensitivity and reciprocity	Direct observation of parent and child in free-play, clean-up task, and book-sharing
Parental discipline	Discipline and Violence Self-report Questionnaire
	Direct observation during the prohibition and compliance tasks
Parental mental state talk	Direct observation during interactions involving book-sharing and a narrative cartoon explanation task
Exploratory outcomes	
Home language environment	LENA digital recording device worn by the child for a full day
Emotion recognition	Functional Infared Thermal Imaging (fIRT)
Moderators	
Parental stress	Parenting Stress Index (short form)
Caregiver mental health	Patient Health Questionnaire-9
Intimate partner violence	WHO questionnaire on health and domestic violence

### Primary outcome measures

Child cognition

*Child language*

Child language is assessed by interviewing the primary caregiver with the short form of the MacArthur Bates Communication Development Inventory (CDI) [50]. This 100-item checklist, which has previously been used in other African contexts [51], provides information on child expressive and receptive language. Aggregate scores are calculated and used as interval scale variables. This assessment is made at all three assessment points.

An adapted version of the Peabody Picture Vocabulary Test (PPVT) [52] is used to assess child language comprehension directly, at baseline and post intervention. This consists of 24 items displayed on a screen in groups of four. The child is asked to point or ‘touch’ certain items by the assessor (‘Where is the dog. Show me the dog. Point to the dog’).

For expressive language, a 15-item adapted version of the Expressive One Word Picture Vocabulary Test (EOWPVT) [53] is administered at baseline and post intervention. The child is prompted to say the names of images that are displayed on a screen (‘Look at the picture [child’s name]. What is that? What is that called? Can you tell me what that is?’). Furthermore, the Bayley Scale of Infant Development [54] language subscales will be used. These provide a comprehensive measure of expressive and receptive language abilities and have previously been used in a study in peri-urban Kenya [55].

Both the CDI and the adaptation of the Peabody were used in our previous study evaluating book-sharing, and were found to be sensitive to the intervention and to be related to parenting [45, 46, 49].

*Child attention*

Child attention is measured using the Early Childhood Vigilance Task (ECVT) [56]. This is a screen-based assessment of sustained focal attention during which the child views interesting moving cartoon stimuli. The child monitors the screen as images appear, disappear, and then reappear over a period of 7 min. Infant sustained attention is indexed by the number of seconds the child attends to the screen, expressed as a proportion of the 7 min of the video. This assessment is made at all three assessment points. The ECVT has been used successfully in other African contexts [57], as well as in our previous RCT [45, 46].2.Child behaviour

*Child prosocial behaviour*

This is assessed directly in a prosocial ‘helping’ task where a scenario is created that gives the child the opportunity to help the assessor locate her lost pen [46, 58]. ‘Helping behaviour’ is scored if the child picks up the lost pen and returns it to the assessor, or points to the lost pen, or verbally indicates its location to the assessor. This assessment, based on a task reported by Buttelmann and colleagues [58], was used in our previous trial of book-sharing and was found to show effects of the intervention [46].

In addition, the child’s main caretaker is interviewed using the prosocial scale of the Strengths and Difficulties Questionnaire (SDQ) [59], a measure that has previously been used successfully in South Africa [60]. This is a five-item subscale, that uses a 3-point Likert scale that can be aggregated and used as an interval scale variable of raw scores. This assessment is made at all three assessment points.

*Child aggression*

The child’s main caregiver is interviewed using the aggression subscale of the Child Behavior Checklist (CBCL) for ages 18 months to 5 years [61]. This is a 20-item questionnaire that uses a 3-point Likert scale on which children are rated according to various types of aggressive and defiant behaviour. An aggregate of raw scores is used as an interval scale variable that can be dichotomised. This measure has been used successfully in several South African studies [62–64].

Direct measures of child aggression and defiance/noncompliance are obtained from coded video data of two parent-child interaction tasks: a ‘Don’t touch’ prohibition task, and a ‘Clean up’ compliance task [65–67], and one frustration task – the ‘Barrier’ task. The first two tasks have been used to assess child defiance in several HICs [66, 67]. Since they have, to our knowledge, not been used in LMIC contexts, baseline videos will be examined and culturally sensitive modifications will be made to existing coding schemes. The Barrier task has also been widely used in HICs [68], as well as in our previous work in South Africa [69], to provide a measure of negative reactivity (on the basis of latency (3-point scale) and intensity (5-point scale) of negative emotion), and constructive versus nonconstructive emotion regulation strategy.

